## Abstract

**Background:** BuqiTongluo (BQTL) granules are herbal phenotypic drugs for Qi deficiency and blood stasis (QDBS) syndrome. Its discovery relied primarily on knowledge of observable phenotypic changes associated with diseases. Although BQTL granules have been widely advocated by Chinese Medicine (CM) practitioners, its use lacks empirical support.

**Aim of the study:** In this basket trial, the efficacy of BQTL granules in multiple diseases that have the QDBS syndrome in common will be compared with placebo.

**Materials and Methods:** The BuqiTongluo granule for Qi deficiency and blood stasis syndrome (BOSS) study is a basket herbal trial (ClinicalTrials.gov, NCT04408261). It will be a double-blinded, randomized, placebo-controlled, parallel, multicenter, clinical trial. In total, 432 patients (1:1:1 ischemic stroke, stable angina pectoris, and diabetic peripheral neuropathy), who meet the operationalized diagnostic criteria for QDBS syndrome, have been recruited and randomized in a ratio of 1:1 to receive 6 weeks’ treatment with BQTL granules or placebo. The primary outcome is the change in the QDBS syndrome score at week 6 from baseline. Secondary outcomes include objective outcome measures for the three diseases and adverse events. Omics will help to understand these responses by molecular events.

**Conclusion:** QDBS syndrome is a common phenotypic marker that was hypothesized to predict whether patients with multiple diseases would respond to this targeted therapy. No previous basket trial has assessed the potential efficacy of an herbal intervention for multiple diseases. The unique promise of the trial is its ability to exploit a disease phenotype to discover novel treatments for three diseases for which the root cause is unknown, complex, or multifactorial, and for which scientific understanding is insufficient to provide valid molecular targets.

## Introduction

Implementation of innovative design strategies in the development of efficacious and safe herbal medicines is of major interest to patients, the pharmaceutical industry, and regulators. In China, the National Medical Products Administration (NMPA) has supported various joint efforts to develop new methodologies for increasing the efficiency of clinical trials in complicated diseases. These design strategies include integrated herbal medicine protocol designs, as well as another closely related emerging concept, the basket trial design (Yuan, 2021). The term “basket trial” refers to a design developed to enroll individuals with multiple diseases and one (or a combination of) drug targets in cohorts within a trial (Cunanan et al., 2017). Basket designs have been applied positively in oncology trials dealing with multiple types of cancer (Park et al., 2020).

In Chinese Medicine (CM) theory, multiple diseases in different people may be treated in the same manner (Zhai et al., 2020). Under this treatment principle, the same strategy is used to treat patients with multiple diseases who have the same syndrome (Zheng) (Jiang et al., 2014). Such syndromes provide a massive amount of information in terms of herbal products and the clinical symptoms for which they are used therapeutically, which are the observable disease phenotypes that are crucial for clinical diagnosis and treatment (Miao et al., 2012). The change in the syndrome reflects either remission or progression of the disease.

We have adopted the concept of innovative basket trial design beyond the field of cancer research and have now developed a Phase II herbal trial protocol for treatment of patients with ischemic stroke, stable angina pectoris, and diabetic peripheral neuropathy, who share the same syndrome target [Qi deficiency and blood stasis (QDBS) syndrome] for herbal therapy. QDBS syndrome is one of the basic CM syndromes that is most strongly related to various diseases, including vascular, cardiovascular, and cerebrovascular diseases, and guides the use of herbal medicine (Zhai et al., 2020). It is a common and core pathogenesis of multiple diseases (Li et al., 2007), with a cluster of symptoms, including fatigue, shortness of breath, reticence to speak, spontaneous sweating, pale or dark complexion, local stabbing pain, pale purple tongue, or pale dark tongue. QDBS syndrome is thought to be the basic pathogenesis of ischemic stroke (Fan et al., 2014), coronary artery disease (Hui et al., 2010), and diabetic peripheral neuropathy (Miao et al., 2003) according to CM. Previous studies have demonstrated that changes in the phenotype of QDBS syndrome in patients with ischemic stroke, coronary artery disease, and diabetic peripheral neuropathy were associated with improvement in both symptoms and clinical outcomes of these three diseases (Zhou and Wang, 2014). Herbal medicine adopts a broad pharmacological approach to treat complicated diseases, by deploying a combination of herbal medicines with different treatment effects.

BuqiTongluo (BQTL) granule is a typical herbal formulae created by [name], a famous Chinese medical scientist, to tonify Qi and promote blood circulation (Xie, 2020). The herbal formulae originates from Yi Lin Gai Cuo (Correcting the Errors in the Forest of Medicine) (Wang, 2007). It is composed of eight herbs, including Hedysarum polybotrys Hand.-Mazz (Hongqi), Panax notoginseng (Burkill) F.H.Chen (Sanqi), Alisma plantago-aquatica subsp. orientale (Sam.) Sam (Zexie), Angelica sinensis (Oliv.) Diels (Danggui), Ligusticum chuanxiong Hort (Chuanxiong), Periostracum Cicadae (Chantui), Curcuma aromatica Salisb (Yujin), Neolitsea cassia (L.), Kosterm (Guizhi). Now CM physicians often apply BQTL herbal formulae to treat nerve damage, cardiovascular and cerebrovascular diseases in clinical practice.

Among the herbs cited above, Hedysarum polybotrys Hand.-Mazz. contributes to regulating Qi. According to the Chinese medicine compatibility theory of “sovereign, ministerial, adjuvant and messenger”, the Hedysarum polybotrys Hand.-Mazz is sovereign herb in the BQTL, and it also showed pharmacological activity in well designed experiments. Hedysarum polybotrys polysaccharide (HPS) has significant protective effect against heart and brain hypoxia (Dong et al., 2013). It can protect the endomembrane barrier (Wang et al., 2013), promote peripheral nerve regeneration and improve the recovery of nerve function (Wei et al., 2009), and enhance nerve amplification effect by encouraging proximal axons to grow more lateral buds and effectively improve peripheral nerve (Wang et al., 2013). Panax notoginseng saponins (PNS) is isolated from the roots and rhizomes of Panax notoginseng (Burkill) F.H.Chen, a highly valued Chinese materia medica with the efficacy of promoting blood circulation and removing blood stasis. PNS has been shown to exert strong anti-inflammatory effects against atherosclerosis-related cardiac-cerebral vascular disease (Wan et al., 2009). A new study also suggested that PNS exerted long-term neuroprotective effects that assisted in stroke recovery (Zhou et al., 2021). PNS ameliorates diabetic peripheral neuropathy by attenuating electrophysiological, circulatory and morphological alterations (Hao et al., 2017).

Taken together, BQTL herbal formulae has been widely used to treat multiple diseases involving the QDBS syndrome. However, no large, randomized trial has studied the effect of BQTL granules on QDBS syndrome. The aims of this basket randomized controlled trial (RCT) are firstly to optimize parameters and examine the feasibility of a subsequent phase III RCT through preliminary evidence on the clinical efficacy and safety of BQTL granules on three diseases (ischemic stroke, stable angina pectoris, and diabetic peripheral neuropathy) involving QDBS syndrome, as compared with placebo. Secondly, it aims to elucidate the mechanism by which BQTL granules exert an effect on QDBS syndrome.

## Materials and Methods

### Study Design

The BuqiTongluo granule for Qi deficiency and blood stasis syndrome (BOSS) study is a basket herbal trial studying the effect of BQTL granules across multiple cohorts of three diseases (ClinicalTrials.gov, NCT04408261). The BOSS protocol includes three multicenter randomized, double-blinded, placebo-controlled sub trials that will study BQTL granules in three independent patient populations: ischemic stroke (sub trial I), stable angina pectoris (sub trial II), and diabetic peripheral neuropathy (sub trial III). This study is currently open at 14 sites across China. In each sub trial, patients will be randomly divided into an intervention group (BQTL granule) and placebo group (placebo) using an 1:1 allocation ratio, adhering to the Standard Protocol Items: Recommendations for Interventional Trials (SPIRIT) statement (Chan et al., 2013). The study period includes 6 weeks of medication and 90 days of follow-up. The study procedure is summarized in the CONSORT diagram (Figure 1), and the schedule of enrolment, interventions, and assessments is summarized in Table1. The trial will be performed in accordance with the Declaration of Helsinki and Good Clinical Practice Guidelines. Informed consent will be obtained from all participants.

**FIGURE 1 F1:**
[figure not shown]
The flowchart of participants disposition throughout the study.

**TABLE 1 T1:** The schedule of enrolment, interventions, and assessments in the BOSS trial.
[figure not shown]

Note.

a Eligibility screen: Including inclusion and exclusion criteria, HbA1c, pregnancy test. Only patients with diabetic peripheral neuropathy will be tested for HbA1c, and only fertile women will be tested for blood pregnancy test within 24 h before the first medication.

b Vital signs: Including temperature, respiration, pulse and blood pressure.

c Laboratory examination: Including Routine Blood Examination (RBC, WBC, HGB, PLT, NEU, NE%) , Routine Urine Examination (GLU, LEU, PRO, KET, BLD, SG, pH) , Routine Stool Examination (RBC, WBC, fecal occult blood) , Blood Lipid Examination (TC, TG, LDL, HDL) , FBS, Electrolyte Examination (Na, K, Cl, Ca, P) , Liver Function (ALT, AST, GGT, ALP, TBIL) , Renal Function (BUN, Cr) , Coagulation Function (PT, APTT, TT, FIB, INR). Patients with diabetic peripheral neuropathy will also be tested for Urine Microalbumin and Urine NAG. During the trial, the investigator can decide whether to increase the safety indicator test items and times according to patients’ condition.

d Evaluation Scale of Qi Deficiency and Blood Stasis Syndrome, VAS and SF-36 Quality of Life Scale are applicable to all subjects.

e NIHSS, mRS and BI evaluation are only applicable to subjects with convalescence of ischemic stroke.

f SAQ evaluation is only applicable to subjects with stable angina pectoris of coronary artery disease.

g TCSS evaluation is only applicable to subjects with diabetic peripheral neuropathy.

h Concomitant medication: During the screening period and the whole process of the trial, antihypertensive agents are allowed to be used for blood pressure control. The concomitant medication will be recorded from 3 months before enrollment to the end of the trial.

i Serum specimen collection: The blood samples of 1/3 subjects (ie., the subjects with tongue and facial images collection) will be collected. The collection, processing and storage of blood samples will be carried out according to the “SOP for collection and management of clinical serum samples.”

j Tongue and facial images collection: All the subjects will use the mobile phone APP for tongue and facial images collection. And 1/3 subjects will use the TCM Tongue and Facial Imaging and Analysis Instrument for tongue and facial images collection.

k About D56: It refers to the 14th day after drug withdrawal.

l About D90: It refers to the 90th day after onset for subjects with convalescence of ischemic stroke, and refers to the 90th day after medication for subjects with stable angina pectoris of coronary artery disease and diabetic peripheral neuropathy.

### Participants

For inclusion, all participants will have a diagnosis of QDBS syndrome and should be aged from 35 to 80 years. QDBS syndrome follows the Guideline for clinical research of new Chinese medicine (The State Drug Administration, 2002).

For the ischemic stroke trial (sub Trial I), patients will be diagnosed with ischemic stroke (Sacco et al., 2013), with an interval from onset to recruitment of 14–30 days, and will have a National Institutes of Health Stroke Scale (NIHSS) score ≥4 and ≤22 (Kasner, 2006). Patients will be excluded from sub Trial I if they have a confirmed secondary stroke caused by tumors, brain trauma, or hematological diseases by clinical examination. Patients with other conditions that lead to motor dysfunction (e.g., lameness, osteoarthrosis, rheumatoid arthritis, gouty arthritis), which render a neurological function examination unlikely, will also be excluded.

In the stable angina pectoris trial (sub Trial II), patients will be included if they are diagnosed with stable angina pectoris and have a Canadian Cardiovascular Society classification of Angina Pectoris class I‒III (Knuuti et al., 2020). Patients will be excluded from this trial if they have had acute coronary syndrome or unstable angina pectoris in the previous 3 months, or have other heart diseases (e.g., cardiomyopathy, pericardial disease) such as severe cardiopulmonary insufficiency (congestive heart failure NYHA class IV, severe abnormal pulmonary function), or severe arrhythmias (e.g., rapid atrial fibrillation, atrial flutter, paroxysmal ventricular tachycardia).

In the diabetic peripheral neuropathy trial (sub Trial III), patients with a diagnosis of diabetic peripheral neuropathy will be included (Executive summary, 2014). Patients will be excluded if they have HbA1c >10% during the screening period, have had acute, critical diabetes mellitus conditions in the previous 3 months (e.g., hyperglycemia and hypertonic syndrome, diabetic lactic acidosis, diabetic ketoacidosis), or have severe heart disease, brain disease, or kidney disease. Moreover, patients with spinal cord injury, cervical or lumbar vertebral disease (nerve root compression, spinal stenosis, cervical or lumbar vertebra degenerative disease), or sequelae of cerebrovascular disease, neuromuscular junction, or muscular disease; or neuropathies caused by other diseases (e.g., Guillain-Barré syndrome, chronic inflammatory demyelinating polyneuropathy (CIDP), Vitamin B deficiency, hypothyroidism, alcoholism, or severe arteriovenous vasculopathy such as venous embolism, lymphangitis) will be excluded.

Additionally, patients with uncontrolled hypertension (systolic blood pressure ≥160 mmHg or diastolic blood pressure ≥100 mmHg), or renal or hepatic insufficiency (hepatic insufficiency defined as an alanine aminotransferase (ALT) or aspartate aminotransferase (AST) value that is 1.5 times the upper limit of normal; renal insufficiency defined as a serum creatinine concentration value that is above the upper limit of normal) will be excluded from all trials. Patients with other conditions or mental disorders that, according to the judgment of investigators, would restrict evaluation of mental function or render outcomes or follow-up unlikely to be assessable will also be excluded. Furthermore, pregnant or lactating women, or women who are planning a pregnancy within the next few years, patients who are allergic to the study drug or have a severely allergic constitution, those with a yellow, thick, slimy tongue coating, and those who have participated in other drug or device clinical trials in the past 3 months will also be excluded from all trials.

### Sample Size

For a main phase II trial assessing natural drugs, according to the NMPA recommendation (No. 28, 2007 and No. 109, 2018) and data from our pilot study, the sample size should not be less than 60 per treatment arm for each disease to estimate the parameter. We enrolled 432 participants to allow for dropouts.

### Recruitment

A total of 432 patients who fulfill the screening criteria will be recruited at 14 Good Clinical Practice (GCP)-approved hospitals in China. Local advertisements will be used for recruitment. A contract research organization will help to monitor the on-schedule recruitment progress and take measures in a timely manner. Investigators will provide research information, such as the purpose, the procedures, the potential risks and benefits of participants through standardized interviews before their participation. Written informed consent will then be obtained from all participants.

### Randomization, Allocation Concealment, and Blinding

All eligible patients who consent to participation will be randomized into either the BQTL granule group or the placebo group in an 1:1 ratio. A random sequence table will be generated by using Strategic Applications Software (SAS, version 9.4, SAS Institute, Inc., Cary, NC, United States), and randomization will be conducted using a central web-based interactive randomization service system (CIMS, Chengdu, China) with permuted blocks. The system automatically randomizes patients and generates the randomization code and drug code corresponding to the assigned treatment. The system will not release the randomization code until the patient has been recruited into the trial to ensure allocation concealment. Randomization will be conducted without any influence from research clinicians. All participants, physicians, nurses, data managers, statisticians, and other staff will be blinded to the treatment allocations until the trial is completed. In case of emergency, the principal investigator of each center, who has the only authority to view the blind codes, can log into the central randomization system for emergency unblinding. To ensure the implementation of blinding, the placebo will be identical to the BQTL granule in physical appearance, sensory perception, packaging, and labeling, and will have no pharmaceutical activity.

### Drug Administration

The BQTL granules contained Hedysarum polybotrys Hand.-Mazz (Hongqi), Panax notoginseng (Burkill) F.H.Chen (Sanqi), Alisma plantago-aquatica subsp. orientale (Sam.) Sam (Zexie), Angelica sinensis (Oliv.) Diels (Danggui), Ligusticum chuanxiong Hort (Chuanxiong), Periostracum Cicadae (Chantui), Curcuma aromatica Salisb (Yujin), and Neolitsea cassia (L.), Kosterm (Guizhi). The criteria for the quality of these ingredients were in accordance with the 2015 Chinese pharmacopoeia. Eligible patients will receive BQTL granules or placebo (10 g) (Table 2) dissolved in boiled water, administered orally three times a day for 6 weeks (one sachet per time). The study drug will be prepared by Shaanxi Buchang Pharmaceuticals Co., Ltd., China. The quality control of the production process strictly adhered to the good manufacturing practice (GMP) of national drug production.

**TABLE 2 T2:** Standard formulation of BuqiTongluo Granule.

Pinyin name	Scientific name	Proportion (g)
Hongqi	Hedysarum polybotrys Hand.-Mazz	500
Sanqi	Panax notoginseng (Burkill) F.H.Chen	100
Zexie	Alisma plantago-aquatica subsp. orientale (Sam.) Sam	333
Danggui	Angelica sinensis (Oliv.) Diels	333
Chuanxiong	Ligusticum chuanxiong Hort	200
Chantui	Periostracum Cicadae	100
Yujin	Curcuma aromatica Salisb	200
Guizhi	Neolitsea cassia (L.) Kosterm	100

### Interventions

Eligible patients will be randomized in equal proportions between the BQTL granule groups and placebo groups, receiving either BQTL granules or placebo. The granules will be dispensed through the clinical trial pharmacies of the 14 hospitals, complying with the standard of pharmacy practice. Two fully registered CM practitioners will be responsible for clinical diagnosis and prescription. During the trial, it will be forbidden to use acupuncture, CM decoctions (compound granules), Chinese medicine injections, Chinese patent medicines (including external use), and external washing with traditional Chinese medicine and health products with a composition or efficacy similar to the study drug. Participants will be allowed to accept standard rehabilitation treatment and use necessary drugs that do not affect the evaluation of study parameters for concomitant diseases. The use of drugs should be standardized according to the guidelines, and the name, dosage, times, and time of use must be recorded for analysis and report.

### Primary Outcomes

The primary outcome of the study is improvement in QDBS syndrome, defined as a change in the national approved QDBS syndrome evaluation scale from before to after the 6-week treatment. The QDBS syndrome evaluation scale (Wang et al., 2015) was chosen because of its practical use in the evaluation of the QDBS syndrome. The scale is a 21-item clinician-rated scale with anchored item descriptions. It lists 21 clinical symptoms and physical signs related to the QDBS syndrome. The scale ranges from 0 to 51 with 51 indicating the worst score possible. The higher the score, the more severe the degree of the syndrome. The scale has been developed, validated, and applied in the Department of Neurology, Cardiology, Endocrinology, and multiple investigators have used this method to assess patients with QDBS syndrome. This scale has excellent inter-rater reliability and internal consistency. It is NMPA’s recommended outcome measure in Guideline for clinical research of new Chinese medicine drugs with syndrome.

### Secondary Outcomes

For sub Trial I, secondary outcomes will be the following: Neurological impairment will be evaluated using the NIHSS (Time Frame: baseline, and on days 14, 28, and 42 during treatment). Self-rating symptoms will be evaluated using a visual analog scale (VAS) (Bijur et al., 2001). This will include VAS scores for limb numbness, swelling of hands or feet, and spontaneous sweating (hemilateral sweating) (Time Frame: baseline, and on days 14, 28, and 42 during treatment, as well as at day 14 after treatment). Continuous changes in the Modified Rankin Scale score (Uyttenboogaart et al., 2005) (Time Frame: baseline, at day 42 during treatment, and at day 90 after onset) will also be recorded. Activities of daily living will be measured using the Barthel Index (BI) score (Uyttenboogaart et al., 2005) (Time Frame: baseline, at day 42 during treatment, and at day 90 after onset).

For sub Trial II, secondary outcomes will include the following: Changes in the Seattle Angina Questionnaire (SAQ) score (Time Frame: baseline, at day 28 during treatment, at day 14 after treatment, and at day 90 after recruitment). Self-rating symptoms will be evaluated using a VAS for chest tightness, chest pain, palpitation, fatigue, and spontaneous sweating (Time Frame: baseline, and on days 14, 28, and 42 during treatment, as well as at day 14 after treatment).

In sub Trial III, the secondary outcomes will be as follows: Changes in the Toronto Clinical Scoring System (Bril and Perkins, 2002) (Time Frame: baseline, and on days 14, 28, and 42 during treatment, day 14 after treatment, as well as day 90 after recruitment). Self-rating symptoms will be evaluated using a VAS for local pain, limb numbness, and paresthesia (e.g., burning sensation, formication, electrical sensation) (Time Frame: baseline, and on days 14, 28, and 42 during treatment, as well as at day 14 after treatment).

For all sub trials, quality of life will be measured as a secondary outcome, using the 36-Item Short Form Survey (SF-36) (Time Frame: Baseline, at day 42 during treatment, and at day 90 after onset/recruitment). Blood, urine, and feces samples will be collected at baseline and day 42 for metabolomics, proteomics, microbiota, and flow-cytometry studies.

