### Statistical Methods

Statistical analysis will be performed using Statistical Analysis System version 9.4 (SAS Institute Inc., Cary, North Carolina, United States) statistical software packages. Outcome measurements will be analyzed using full analysis sets and per protocol sets according to intention-to-treat (ITT) analysis. Safety analysis will be performed in a safety set, which is defined as a subset of subjects who received at least one treatment and had actual safety indicators record data. The statistical analysis will include baseline characteristics of participants, compliance and concomitant medication, efficacy analysis and safety analysis. For continuous data, we will describe the results using the mean (standard deviation, SD), maximum, minimum, median and non-parametric test median (quartile deviation, QD). Categorical data will be described as absolute values and proportions. For continuous outcomes, paired *t*-test or Wilcoxon signed-rank test will be used to analyze significant differences between baseline and each time point. The Wilcoxon rank-sum test will be employed for comparisons between treatment groups. Chi-squared test will be used for categorical data and Wilcoxon rank-sum test will be used for ranked data. Analysis of covariance (ANCOVA) will be used to control potential confounding variables.

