We will use a two-sided 5% significance level and 85% power. Baseline characteristics in each group will be analyzed using descriptive statistics. Compliance analysis will be based on full analysis sets, and analysis of concomitant medications will be based on safety sets. Regarding the primary outcome variable, between-group comparisons of the change in syndrome score will be analyzed between pre- and post-treatment using paired t-test or Wilcoxon signed-rank test. As to the secondary outcomes, comparisons of the changes in NIHSS score in sub Trial I, the Seattle Angina Questionnaire score in sub Trial II, and the Toronto Clinical Scoring System in sub Trial III, will be analyzed using paired t-test or Wilcoxon signed-rank test between baseline and each time point. The Wilcoxon rank-sum test will be employed for comparisons between treatment groups. Any factors impacting efficacy, such as age and sex, should be taken into account as covariate. Safety will be analyzed in terms of all the adverse events occurred during the trial, and the incidence will be compared between groups using the chi-squared test or Fisher’s exact probability method.

Last observation carry forward (LOCF) approach will be used to impute missing data of primary outcome according to intention-to-treat analysis. A sensitivity analysis will be conducted to determine the robustness of the results under the missing at random assumption, to evaluate the role of lost to follow-up (i.e., participants who did not follow-up to V4), by using the LOCF method. And a *p* value of less than 0.05 will be considered statistically significant.

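### Symptom VAS items are scored in all patients, but entry does not require each symptom; baseline zeros dilute the unadjusted comparison by an amount that depends on unstated prevalence

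*Protocol article*

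**What the plan says.** - **Items.** Secondary Outcomes lists three VAS items for stroke ("This will include VAS scores for limb numbness, swelling of hands or feet, and spontaneous sweating (hemilateral sweating"), five for angina (chest tightness, chest pain, palpitation, fatigue, spontaneous sweating) and three for neuropathy (local pain, limb numbness, paresthesia): 11 in all.
- **Who is scored.** Table 1, note d: "Evaluation Scale of Qi Deficiency and Blood Stasis Syndrome, VAS and SF-36 Quality of Life Scale are applicable to all subjects".
- **Entry.** Participants requires a QDBS diagnosis, age 35 to 80 and the disease criteria (for stroke, NIHSS 4 to 22). It names no VAS item and no minimum VAS. The Introduction describes fatigue, spontaneous sweating and local stabbing pain as part of the syndrome's symptom cluster, without saying that each must be present.
- **Analysis.** Statistical Methods assigns outcome measurements to the full analysis and per protocol sets, and says "The Wilcoxon rank-sum test will be employed for comparisons between treatment groups". It names no symptomatic subset. ANCOVA is planned to control confounders, and age and sex are the example covariates. Baseline VAS is not mentioned.

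**The concern.** A patient without hand swelling or palpitation at baseline scores 0 on that item and can only stay there or worsen. Taken together, the scoring rule, the entry criteria and the analysis sets put this patient into the change comparison with full weight. Patients who stay at zero give identical no-change values in both arms.

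Two things follow. The estimated difference becomes a mix of relief in those who had the symptom and fixed zeros in those who did not, so its size depends on how common the symptom is. And an unadjusted rank test loses power, because the gap between symptomatic and symptom-free patients acts as noise. This matters because one stated aim of the trial is to optimise parameters for a phase III trial, and the Discussion gives the VAS a prominent place in reporting. A real effect on an uncommon symptom could be read as no effect, and a VAS difference or SD taken from all patients would not describe patients who have the symptom.

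**Working it through.** **The plan's own figures.** Sample Size says "the sample size should not be less than 60 per treatment arm for each disease to estimate the parameter" and "We enrolled 432 participants to allow for dropouts". The Abstract splits the 432 equally over three diseases, and Study Design randomises "using an 1:1 allocation ratio" in each sub trial. So 432 / 3 = 144 per disease and 144 / 2 = 72 per arm. Going from 60 to 72 allows for 1 − 60/72 = 16.7% dropout. Statistical Methods adds "We will use a two-sided 5% significance level and 85% power", with no effect size or SD. The 85% therefore cannot be reproduced, and it is not tied to any VAS item.

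**Dilution of the estimate.** If a share p has the symptom, the difference among them is D, and symptom-free patients stay at 0, the all-patient difference is p × D.

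**Scenario 1 (all inputs assumed).** 72 per arm; 0–10 VAS; baseline mean 5 and SD 1.5 in symptomatic patients; change −1.5 on placebo and −2.5 on BQTL, SD 2; scores floored at 0. The floor reduces D from 1.0 to about 0.88. Simulated power, two-sided 5%:

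| Prevalence p | All-patient difference (about 0.88p) | Wilcoxon, all patients | Wilcoxon, baseline VAS >0 | ANCOVA on baseline VAS, all patients |
|---|---|---|---|---|
| 30% | 0.27 | 15% | 31% | 32% |
| 40% | 0.35 | 21% | 41% | 42% |
| 50% | 0.44 | 30% | 50% | 51% |
| 70% | 0.61 | 50% | 66% | 67% |
| 90% | 0.79 | 70% | 77% | 77% |

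At 100% both Wilcoxon analyses have 80%. Simulation error is about one to two points. The ratio of the third column to the fourth is 15/31 = 0.48, 21/41 = 0.51, 30/50 = 0.60, 50/66 = 0.76 and 70/77 = 0.91.

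**Scenario 2 (a check in SD units).** Set the effect so that power is 85% if every patient has the symptom: d = (1.960 + 1.036) × √(2/72) = 0.499 SD. Let m be the mean placebo improvement in SD units among symptomatic patients. Per-arm variances are v0 = p + p(1−p)m² and v1 = p + p(1−p)(m+d)², and power = Φ(pd / √((v0+v1)/72) − 1.96). Restricting to symptomatic patients leaves 72p per arm with effect d.

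| p | All, m = 0 | All, m = 1 | All, m = 1.5 | Symptomatic only |
|---|---|---|---|---|
| 0.9 | 0.81 | 0.75 | 0.70 | 0.81 |
| 0.6 | 0.62 | 0.44 | 0.34 | 0.64 |
| 0.4 | 0.45 | 0.27 | 0.20 | 0.47 |

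The rank test loses more than this approximation: simulated at m = 1 it gives 0.72, 0.35 and 0.18 for the same p. With 60 per arm and d reset to 0.547, the normal-approximation results agree within 0.01.

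**Reading the two together.** The loss grows as prevalence falls and as placebo improvement grows (scenario 1 corresponds to m = 1.5/2 = 0.75). Part of it cannot be recovered: measured against a trial in which everyone has the symptom, power falls to half of 85% at p = 0.38, 0.58 or 0.69 for m = 0, 1 or 1.5, but the symptomatic-only analysis loses power as well. The avoidable part is the gap between the all-patient and symptomatic-only columns.

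**The case against.** Several points on the other side stand.

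- **The all-patient comparison is valid.** It keeps its type I error, follows the intention-to-treat principle and estimates the effect in the enrolled QDBS population. A phase III trial with the same entry criteria could want that estimate. A reader might infer that the analysis is biased; it is not.
- **Restriction is not the only way to recover power.** ANCOVA on the item's baseline in all patients does as well (last column of the first table). It does not undo the dilution of the estimate, which remains about p × D.
- **Exposure differs by item.** Diagnosed angina makes chest pain or tightness likely, diagnosed neuropathy makes numbness, pain or paresthesia likely, and fatigue and sweating belong to the syndrome cluster. The content of the cited QDBS criteria is not shown. One prevalence range cannot be applied to all 11 items.
- **Zeros carry some information**, since those patients can worsen.
- **The VAS analysis is partly inferred.** Note d sits in the assessment schedule, and the paragraph naming the NIHSS, SAQ and Toronto comparisons omits the VAS, so only the general rule for continuous outcomes applies. The full protocol or SAP may define an analysis population for each item. Its absence from an article is no finding. The point rests on what is stated: scoring of all subjects, the two analysis sets and an unadjusted rank test.

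**Conclusion.** The concern holds in a limited form. As stated, the VAS comparison includes patients who cannot improve, so the difference shrinks in proportion to symptom prevalence and the unadjusted test loses power. In the first scenario the avoidable loss is 77 − 70 = 7 points at 90% prevalence, 16 at 70%, 20 at 50% and 16 at 30%. It amounts to about half of the attainable power only at roughly 30–40%. With a larger assumed placebo improvement that point moves to higher prevalence; with none, the normal approximation shows almost no avoidable loss. Prevalence, effect, SD and placebo change are all assumptions, as is symptom-free patients staying at 0.

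A reader might infer that power on the VAS items is halved in general. The documents give no prevalence, VAS effect or VAS SD, so they do not support this. Nor do they support any effect on the primary outcome or the sample size: these are secondary outcomes with no stated power. Stroke hand or foot swelling, hemilateral sweating and palpitation are probably most exposed. Severity is low, but the improvement is cheap.

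**What to change.** Before unblinding, for each VAS item:

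1. Keep the all-patient comparison, but adjust it for that item's baseline VAS. ANCOVA is already in Statistical Methods; only the covariate has to be named.
2. Prespecify a comparison in patients with baseline VAS above 0 as the estimate of symptom relief. The subset is defined by a pre-treatment value, so the comparison remains randomised.
3. Report by arm the number of baseline-zero patients and the proportion who develop the symptom.

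The cost is one analysis rule and no new data or visits. The downside is a smaller subset that differs from item to item: at 30% prevalence about 0.3 × 72 ≈ 22 per arm, with power near 31% in the first scenario. The restriction does not restore full power for uncommon symptoms.
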